## 7. DISPOSITION OF PATIENTS

The follow data summaries will be prepared for all subjects allocated to a treatment (ITT).

For the subjects for whom observations are discontinued or completed, the numbers of subjects observed for 1 year and 2 years and frequency distributions of the reasons for discontinuation/completion will be determined for each treatment group.

Discontinuation of observations: When the following criteria for discontinuation/completion are met and observations are discontinued.

Discontinuation/completion criteria

- 1) The subject requests that their study participation be discontinued or withdraws their consent

- 2) A serious adverse events occurs, making continued study participation difficult
- 3) An evaluated event occurs
- 4) The study drug is continuously withdrawn for more than 4 weeks
- 5) The investigator/subinvestigator otherwise determines that the subject's continued study participation would be difficult

## 8. DESCRIPTION OF ANALYSIS SETS

### 8.1 Demographic and other baseline characteristics

Descriptive statistics (no. of subjects, mean, standard deviation, minimum, median, maximum) will be calculated by treatment group for the following variables, and the differences between the groups will be examined using the Wilcoxon test: age, height, weight, BMI, duration of morbidity, blood pressure (systolic and diastolic) on first day of observations, and laboratory values (WBC, RBC, hemoglobin, hematocrit, platelet count, AST, ALT, TC, TG, HDL-C, creatinine, fasting blood glucose, HbA1c).

Frequency distributions for each group will be determined for the variables shown in Table 8.1, and the differences between the groups will be examined using the chi-square or Wilcoxon test.

Table 8.1. Demographic and other baseline characteristics

| Variable                              | Category                                      |
|---------------------------------------|-----------------------------------------------|
| Sex                                   | Male, Female                                  |
| Age                                   | up to 49, 50 to 59, 60 to 69, 70 and older    |
|                                       | up to 64, 65 and older                        |
| Duration of morbidity (days)          | up to 28, 29 to 56, 57 to 112, 113 and longer |
| BMI                                   | < 25, ≥ 25                                    |
| Past history and concomitant diseases |                                               |
| Coronary artery disease               | No, Yes                                       |
| Peripheral artery disease             | No, Yes                                       |
| hypertension                          | No, Yes                                       |
| Diabetes mellitus                     | No, Yes                                       |
| Dyslipidemia                          | No, Yes                                       |

|                                                            |                                               |
|------------------------------------------------------------|-----------------------------------------------|
| Chronic renal disease                                      | No, Yes                                       |
| History of symptomatic ischemic stroke                     | No, Yes                                       |
| Habitual smoking                                           | No, Yes                                       |
| Antiplatelet drug                                          | aspirin, clopidogrel                          |
| Clinical subtype                                           | lacunar, atherothrombotic, other, unknown     |
| Responsible lesion                                         | supratentorial, infratentorial, both, unknown |
| Microbleeds                                                | No, Yes                                       |
| At least 50% stenosis of a major intracranial artery       | No, Yes                                       |
| At least 50% stenosis of an extracranial artery            | No, Yes                                       |
| Chest x-ray                                                | Normal, abnormal                              |
| ECG                                                        | Normal, abnormal                              |
| Degree of independence in activities of daily living (mRS) | 0, 1, 2, 3, 4, 5, 6                           |

## 8.2 Compliance

### 8.2.1 Study drug compliance

A frequency distribution will be determined for study drug [cilostazol and the other antiplatelet drugs (aspirin, clopidogrel)] compliance (compliance  $\geq 70\%$ ,  $<70\%$ , and whether withdrawn) at each timepoint by treatment group.

### 8.2.2 Observation period

- 1) The observation period (person-years) will be calculated for each treatment group.  
The observation period will be the number of days from the first day of observations to the last day (observation end date - observation start date).
- 2) For each group, the observation periods will be classified as being up to 12 months ( $\leq 365$  days), 13 to 24 months (366 to 731 days), 25 to 36 months (732 to 1,096 days), and  $\geq 37$  months (1,097 days or longer), the frequency distribution will be determined, descriptive statistics (no. of subjects, mean, standard deviation, minimum, median, maximum) calculated, and the groups compared using the Wilcoxon test.

### **8.2.3 Compliance for drugs other than study drugs**

Whether drugs were taken for hypertension (beta-blockers, alpha-beta blockers, calcium channel blockers, angiotensin converting enzyme inhibitors, angiotensin II receptor antagonists, diuretics, and other antihypertensive drugs), diabetes (insulin/insulin analogs, non-insulin oral diabetes drugs), or hyperlipidemia (statins, non-statin lipid-lowering drugs) will be summarized for each timepoint and treatment group.

If a drug is used even once after the start of the observations, it will be treated as having been used throughout the study period.

## **9. EFFICACY EVALUATION**

### **9.1 Primary endpoint**

The first recurrence of ischemic stroke between the first and last observation days (during the observation period) will be included in the analysis.

Subjects discontinued for reasons other than occurrence of the primary endpoint and subjects who continue to study completion will be treated as censored subjects. The censor date will be considered the observation completion date.

- 1) A between-groups comparison for the period from the observation start date to the date of ischemic stroke recurrence will be performed using the log-rank test, and the superiority of the combination therapy group versus the monotherapy group will be examined.
- 2) Survival coefficients for the period from the observation start date to the date of ischemic stroke recurrence will be estimated for each treatment group using the Kaplan-Meier method and plotted.
- 3) The hazard ratio for ischemic stroke recurrence in the combination therapy group versus the monotherapy group and its 95% confidence interval will be determined using a Cox proportional hazard model.
- 4) An adjusted hazard ratio will be calculated using a Cox proportional hazard model that includes as covariates age (each 1 year), sex, ischemic stroke clinical subtype (atheromic, lacunar, other, unknown), mRS (ordered categorical data).
- 5) The annual incidence in each group will be calculated using the person-year and Kaplan-Meier methods. The 95% confidence interval of the incidence will be calculated using the approximate Poisson method and the Greenwood method. One year will be considered 365.25 days for the calculations.

- 6) A subgroup analysis will be performed for each variable shown in Table 6.8 using a Cox proportional hazard model that includes a comparison group and predictive factors. The hazard ratio for the combination therapy group versus the monotherapy group will be calculated for each stratification category based on the predictive factors. Uniformity will be examined for the stratification categories based on the interaction between the comparison group and predictive factors.
- 7) Frequency distributions for each treatment group will be determined for the findings regarding the clinical subtype of ischemic stroke (lacunar, atherothrombotic, other, unknown) and responsible lesion (supratentorial, infratentorial, both, unknown) at the time of ischemic stroke onset.

## **9.2 Secondary endpoints**

The secondary endpoints will be those indicated below. Events or accidents that occur between the observation start date and the observation end date (during the observation period) will be included in the analysis.

1. Stroke (ischemic stroke, intracerebral hemorrhage, subarachnoid hemorrhage)
2. Intracerebral hemorrhage or subarachnoid hemorrhage
3. Ischemic cerebrovascular disorder (ischemic stroke, TIA)
4. Death from any cause
5. Stroke (ischemic stroke, intracerebral hemorrhage, subarachnoid hemorrhage), myocardial infarction, or vascular death
6. All vascular events: stroke, myocardial infarction, and other vascular events [e.g., aortic dissection or rupture; pulmonary embolism; heart failure, angina pectoris, or occlusive arteriosclerosis requiring hospitalization; and revascularization (e.g., coronary artery, aorta, peripheral artery)]

### **9.2.1 Stroke (ischemic stroke, intracerebral hemorrhage, subarachnoid hemorrhage)**

The first event involving ischemic stroke, intracerebral hemorrhage, or subarachnoid hemorrhage will be included in the analysis.

Subjects discontinued for reasons other than occurrence of an event included in the analysis and subjects who continue to study completion will be considered censored subjects. The censor date will be considered the observation completion date.

- 1) A between-groups comparison for the period from the observation start date to the date of ischemic stroke onset will be performed using the log-rank test, and the superiority of the combination therapy group versus the monotherapy group will be examined.
- 2) Survival coefficients for the period from the observation start date to the date of the event will be estimated for each treatment group using the Kaplan-Meier method and plotted.
- 3) The hazard ratio for the occurrence of an event in either of the 2 groups and its 95% confidence interval will be determined using the Cox proportional hazard model.

The same analysis described in section 9.2.1 will be performed for the events indicated in sections 9.2.2 to 9.2.6.

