### **9.2.2 Intracerebral hemorrhage or subarachnoid hemorrhage**

The first event involving intracerebral hemorrhage or subarachnoid hemorrhage will be included in the analysis.

Subjects discontinued for reasons other than occurrence of an event included in the analysis and subjects who continue to study completion will be considered censored subjects. The censor date will be considered the observation completion date.

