### **9.2.3 Ischemic cerebrovascular disorder (ischemic stroke, TIA)**

The first event involving ischemic stroke or TIA will be included in the analysis.

Subjects discontinued for reasons other than occurrence of an event included in the analysis and subjects who continue to study completion will be considered censored subjects. The censor date will be considered the observation completion date.

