### **9.2.4 Death from any cause**

All deaths will be included in the analysis.

Subjects discontinued for reasons other than death, which will be included in the analysis, and subjects who continue to study completion will be considered censored subjects. The censor date will be considered the observation completion date.

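### SAP 9.2.1 writes the any-stroke log-rank test on time to ischemic stroke, against the section's own event definition; 9.2.2 to 9.2.6 inherit the ambiguity

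*Supplement*

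**What the plan says.** SAP 9.2.1 covers the secondary endpoint of any stroke. It opens by fixing the event: "The first event involving ischemic stroke, intracerebral hemorrhage, or subarachnoid hemorrhage will be included in the analysis". Subjects discontinued for any reason other than such an event, and those followed to study completion, are censored at the end of observation. Three analyses follow:

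- Item 1), log-rank: the comparison "from the observation start date to the date of ischemic stroke onset will be performed using the log-rank test".
- Item 2), Kaplan-Meier: "Survival coefficients for the period from the observation start date to the date of the event will be estimated for each treatment group".
- Item 3), Cox: "The hazard ratio for the occurrence of an event in either of the 2 groups and its 95% confidence interval".

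The section ends with a carry-over rule: "The same analysis described in section 9.2.1 will be performed for the events indicated in sections 9.2.2 to 9.2.6". Sections 9.2.2 to 9.2.6 then give an event and a censoring rule each, with no test of their own.

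Nothing else shown supplies a log-rank definition for the secondary endpoints. Protocol v1.3 section 11.3 specifies the log-rank test for the primary endpoint only and leaves details to the statistical analysis protocol. The supplement's contents list describes the SAP as unchanged, and its revision history (section 12) ends at version 1.00.

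**The concern.** Within one section the test runs on one event, and the curve and hazard ratio run on another. Any stroke is the endpoint in which fewer ischemic strokes and more hemorrhagic strokes would offset each other. A log-rank test limited to ischemic stroke cannot show that offset.

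SAP 6.5 sets a two-sided 5% level for the secondary tests, and SAP 6.6 makes no multiplicity adjustment among them. Each p-value will therefore be read at face value. If the plan supports two versions of the any-stroke test, an analyst who has seen the data could defend either. A prespecified plan should close that choice. Because 9.2.1 is the template for the five sections after it, the wording also affects how those are read.

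**Working it through.** The point turns on wording, so the main check sets the statements side by side.

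**Step 1. Event used by each statement in SAP 9.2.1**

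| Statement | Event it points to |
|---|---|
| Section title | ischemic stroke, ICH, SAH |
| Opening definition | first of ischemic stroke, ICH, SAH |
| Censoring rule | anyone without such an event is censored |
| Item 1), log-rank | ischemic stroke only |
| Item 2), Kaplan-Meier | the endpoint event |
| Item 3), Cox | the endpoint event |

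Item 1) is alone. SAP 9.1 item 1), the primary log-rank test, has almost the same sentence, ending at ischemic stroke recurrence. That suggests the phrase was carried over.

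**Step 2. What item 1) does if followed literally**

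- First event ischemic stroke: counted in all three items.
- First event ICH or SAH: counted in items 2) and 3). For item 1) there is no ischemic stroke date. The section's censoring rule does not censor this subject either, because the discontinuation was for an event included in the analysis. A later ischemic stroke would normally go unobserved, since an evaluated event is itself a discontinuation criterion (SAP section 7, criterion 3).
- No stroke: censored at the end of observation in all three items.

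So item 1) can be run only if someone decides what to do with the ICH and SAH subjects. The natural choice is to censor them at the end of observation. The time origin, event and censoring dates are then those of SAP 9.1, and the any-stroke p-value is in essence the primary p-value.

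**Step 3. The sections that inherit item 1)**

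| Section | Its own event | Ischemic stroke a component? | Own log-rank text? |
|---|---|---|---|
| 9.2.2 | "The first event involving intracerebral hemorrhage or subarachnoid hemorrhage will be included in the analysis" | no | no |
| 9.2.3 | "The first event involving ischemic stroke or TIA will be included in the analysis" | yes | no |
| 9.2.4 | "All deaths will be included in the analysis" | no | no |
| 9.2.5 | first stroke, MI or vascular death | yes | no |
| 9.2.6 | first stroke, MI or other vascular event | yes | no |

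The carry-over rule sends the analysis to the events named in those sections. On its plain meaning, the method moves and the event is replaced. What remains unclear is that item 1), unlike items 2) and 3), has no generic event word to replace.

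**Step 4. Numbers**

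The SAP gives one sample-size result, 1,688 per group, for the primary endpoint (SAP section 4). Inputs: 4% and 2.8% per year taken as hazards, accrual A = 2.5 years, total T = 3.5 years, two-sided alpha 0.05, power 80%, no dropout.

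- Events (Schoenfeld): 4(1.960 + 0.842)² / (ln 0.70)² = 31.40 / 0.1272 = 246.8, so 247.
- Event probability: p = 1 − [exp(−λ(T−A)) − exp(−λT)] / (λA). For λ = 0.04, p = 1 − (0.9608 − 0.8694)/0.10 = 0.0857. For λ = 0.028, p = 1 − (0.9724 − 0.9066)/0.07 = 0.0609. The mean is 0.0733.
- Per group: 246.8 / 0.0733 / 2 ≈ 1,684, against the stated 1,688. A numerical Lakatos calculation gives 1,715 (251 events), also within 3%.
- Dropout: 1,688 / 0.95^3.5 = 1,688 / 0.8357 ≈ 2,020, against the stated 2,000.

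None of these figures involves the sentence in 9.2.1. For the secondary endpoints the documents give no rates for ICH, SAH, TIA, death, MI or the composites. The shift in any secondary p-value therefore cannot be calculated.

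**The case against.** The strongest reply is that the intent is plain. In 9.2.1 the title, the opening definition, the censoring rule and items 2) and 3) all point to any stroke, and a single phrase points elsewhere. SAP 6.2.5 derives time to onset separately for each event type, so the data for the right test will exist. A careful programmer would very likely run it. This stands as an argument about risk, and it is why the severity is minor. It does not remove the contradiction: item 1) is the sole log-rank instruction, and no other text shown overrides it for 9.2.1.

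A reader might go further and infer that all six secondary log-rank tests are defined on ischemic stroke. The documents do not support that. The carry-over rule names the events of 9.2.2 to 9.2.6, and each of those sections states its own event and censoring rule.

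A reader might also infer that an excess of hemorrhage or a difference in mortality would go untested. That fails too. Item 3) gives a hazard ratio with a 95% confidence interval for each endpoint on its own event. SAP 10.5 also compares hemorrhagic events by chi-square, including GUSTO severe or life-threatening bleeding, which covers intracranial bleeding.

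Item 1)'s reference to superiority might seem ill-suited to ICH/SAH and death. SAP 6.5 already makes the tests two-sided, so rewording it would change no result.

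**Conclusion.** Wrong as written, minor severity. In SAP 9.2.1 the log-rank event contradicts the endpoint. Taken literally, the any-stroke test loses every ICH and SAH and essentially duplicates the primary test. That conclusion assumes that subjects with ICH or SAH would be censored at the end of observation, and that observation stops at an evaluated event as SAP section 7 states.

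For 9.2.2 to 9.2.6 the fault is an ambiguity taken over from the template, and the better reading already uses each section's own event. The primary analysis, its alpha, the power and the sample size are unaffected.

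**What to change.** In SAP 9.2.1 item 1), replace the end of the interval, now the onset of ischemic stroke, with *the date of the first event included in the analysis*. This matches item 2). Through the existing carry-over sentence, the log-rank, Kaplan-Meier and Cox analyses then share one event definition within each of 9.2.1 to 9.2.6.

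The cost is one phrase in the SAP, made and dated before database lock. No data collection, sample size, power or significance level changes.

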### **9.2.2 Intracerebral hemorrhage or subarachnoid hemorrhage**

The first event involving intracerebral hemorrhage or subarachnoid hemorrhage will be included in the analysis.

Subjects discontinued for reasons other than occurrence of an event included in the analysis and subjects who continue to study completion will be considered censored subjects. The censor date will be considered the observation completion date.

### **9.2.3 Ischemic cerebrovascular disorder (ischemic stroke, TIA)**

The first event involving ischemic stroke or TIA will be included in the analysis.

Subjects discontinued for reasons other than occurrence of an event included in the analysis and subjects who continue to study completion will be considered censored subjects. The censor date will be considered the observation completion date.

### **9.2.4 Death from any cause**

All deaths will be included in the analysis.

Subjects discontinued for reasons other than death, which will be included in the analysis, and subjects who continue to study completion will be considered censored subjects. The censor date will be considered the observation completion date.

### **9.2.5 Stroke (ischemic stroke, intracerebral hemorrhage, subarachnoid hemorrhage), myocardial infarction, or vascular death**

The first event involving ischemic stroke, intracerebral hemorrhage, subarachnoid hemorrhage,

myocardial infarction, or vascular death will be included in the analysis.

Subjects discontinued for reasons other than occurrence of an event included in the analysis and subjects who continue to study completion will be considered censored subjects. The censor date will be considered the observation completion date.

**9.2.6 All vascular events: stroke, myocardial infarction, and other vascular events [e.g., aortic dissection or rupture; pulmonary embolism; heart failure, angina pectoris, or occlusive arteriosclerosis requiring hospitalization; and revascularization (e.g., coronary artery, aorta, peripheral artery)]**

The first event involving stroke, myocardial infarction, or another vascular event [e.g., aortic dissection or rupture; pulmonary embolism; heart failure, angina pectoris, or occlusive arteriosclerosis requiring hospitalization; and revascularization (e.g., coronary artery, aorta, peripheral artery)] will be included in the analysis.

Subjects discontinued for reasons other than occurrence of an event included in the analysis and subjects who continue to study completion will be considered censored subjects. The censor date will be considered the observation completion date.

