### 8.2. Secondary endpoints

The following items are secondary endpoints:

- Any stroke [ischemic stroke (IS), intracerebral hemorrhage (ICH), or subarachnoid hemorrhage (SAH)]
- ICH or SAH
- Ischemic cerebrovascular disorder [IS or transient ischemic attack (TIA)]
- Death from any cause
- Stroke [IS, ICH, SAH], myocardial infarction (MI), or vascular death
- All vascular events: stroke, MI, and other vascular events [e.g. aortic dissection or rupture; pulmonary embolism; heart failure, angina pectoris, or occlusive arteriosclerosis requiring hospitalization; and revascularization of coronary artery, aorta, peripheral artery, etc.]

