**ABBREVIATIONS AND DEFINITIONS**

|                         |                                                                                                                                                                                                                                                                                                                                                                             |
|-------------------------|-----------------------------------------------------------------------------------------------------------------------------------------------------------------------------------------------------------------------------------------------------------------------------------------------------------------------------------------------------------------------------|
| Evaluated events:       | Death, ischemic stroke, intracerebral hemorrhage, subarachnoid hemorrhage, transient ischemic attack (TIA), myocardial infarction, other vascular events (aortic dissection or rupture; pulmonary thrombosis; heart failure, angina pectoris, or occlusive arteriosclerosis requiring hospitalization), revascularization (e.g., coronary artery, aorta, peripheral artery) |
| Observation completion: | Observation is complete when a subject meets the criteria for discontinuation/completion or when 1 year has elapsed from the initiation of observation for last subject enrolled                                                                                                                                                                                            |
| Observation period:     | The period from the start to completion of the observations.                                                                                                                                                                                                                                                                                                                |
| Duration of morbidity:  | Period from the most recent noncardioembolic ischemic stroke to the start of observations                                                                                                                                                                                                                                                                                   |

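### The all-vascular-events endpoint does not name vascular death, so a vascular death with no listed event recorded counts in the narrower composite but is likely to be censored in the broader one

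*Supplement*

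**What the plan says.** Two secondary endpoints sit next to each other in protocol v1.3 section 8.2 and again in SAP 2.2.2, 9.2, 9.2.5 and 9.2.6.

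- **Narrower composite.** The protocol has "Stroke [IS, ICH, SAH], myocardial infarction (MI), or vascular death". SAP 9.2.5 repeats the components and ends "myocardial infarction, or vascular death will be included in the analysis".
- **Broader composite.** The protocol has "All vascular events: stroke, MI, and other vascular events". SAP 9.2.6 counts "The first event involving stroke, myocardial infarction, or another vascular event" and illustrates the last category, after an e.g., with "aortic dissection or rupture; pulmonary embolism; heart failure, angina pectoris, or occlusive arteriosclerosis requiring hospitalization", followed by revascularization. Death does not appear.

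The SAP describes the category of other vascular events differently elsewhere. The entry for evaluated events under Abbreviations and definitions reads "other vascular events (aortic dissection or rupture; pulmonary thrombosis; heart failure, angina pectoris, or occlusive arteriosclerosis requiring hospitalization", with no e.g. before the conditions. SAP 6.2.5 does the same. In both places death is a separate item in the list of evaluated events, as it is in protocol 6.3.3.

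SAP 9.2.6 censors "Subjects discontinued for reasons other than occurrence of an event included in the analysis", along with those who reach study completion, at the observation completion date. Under SAP section 7 and protocol 5.3 any evaluated event, death included, ends observation.

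**The concern.** An endpoint presented as covering all vascular events would be expected to include every event in a narrower vascular composite. Here the most severe component is named in the narrower endpoint and absent from the broader one. A programmer working from the evaluated-event categories would naturally read that omission as deliberate, and would censor a patient whose only event is a vascular death.

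If that happens, a patient who dies of a vascular cause leaves the risk set without an event, while a patient who has a revascularization is counted. Should treatment shift such deaths in either direction, the hazard ratio for 9.2.6 would not register the shift. The results of 9.2.5 and 9.2.6 could then not be read as a smaller and a larger version of the same quantity.

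**Working it through.** The plan states no figure on this point, so the check is textual: take each kind of vascular death and follow it through the two rules.

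**Inputs.** Components from SAP 9.2.5, SAP 9.2.6 and protocol 8.2; evaluated-event categories from the SAP definitions, SAP 6.2.5 and protocol 6.3.3; the censoring rule from SAP 9.2.6; the end of observation from SAP section 7.

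1. **Fatal stroke or fatal MI.** An event in both composites, because the stroke or MI is itself a component of each.
2. **Fatal aortic dissection or rupture, or fatal pulmonary embolism.** An event in 9.2.6 through the listed condition. The SAP definitions and 6.2.5 write pulmonary thrombosis where the endpoint text writes pulmonary embolism, which is a further sign that the lists were not aligned.
3. **Death after heart failure, angina or occlusive arteriosclerosis that required hospitalization.** An event in 9.2.6 through that listed event.
4. **Death judged vascular with no listed event recorded**, for example sudden cardiac death or heart-failure death without hospitalization. An event in 9.2.5 as vascular death and in 9.2.4 as a death. In 9.2.6 there are two readings:
   - If the category is closed, as the SAP definitions and 6.2.5 suggest, no included event has occurred. Death ends observation, and the patient is censored on the date of death.
   - If the category is open, as the e.g. in protocol 8.2, protocol 6.3.3 and SAP 9.2.6 suggests, inclusion depends on someone deciding that the death is itself another vascular event. No rule for that decision is written down.

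**Result.** Cases 1 to 3 cause no difficulty. Case 4 alone is enough to break containment: such a patient is certainly an event in 9.2.5 and not certainly an event in 9.2.6. Because the categories used to derive event times keep death apart from other vascular events, censoring is the more likely outcome in practice.

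**Can the endpoint be completed from existing data?** Yes. Protocol 6.3.3 already collects the date and cause of each death and the reason for assigning that cause. Endpoint 9.2.5 cannot be analysed without a classification of deaths as vascular or not. Neither document defines vascular death, so that classification has yet to be written down.

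**The case against.** The strongest reply is that the exclusion is inferred, not stated. Every passage that defines the endpoint introduces its examples with e.g. The closed wording appears only in a glossary entry and in a rule for computing days to onset. Those two passages also disagree with each other: the glossary places revascularization outside the other-vascular-events bracket and 6.2.5 places it inside. The Event Evaluation Committee (protocol 27.4) reviews endpoint events and could accept a sudden cardiac death as another vascular event. This stands to the extent that censoring is likely rather than certain. It does not remove the problem, because an open category leaves the handling of a fatal event to judgement case by case. Protocol 4.1 tells investigators the allocated group, so a component is better fixed in writing.

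A second reply is that nothing is lost to the trial. Vascular death is analysed in 9.2.5 and every death in 9.2.4, both with a log-rank test and a Cox model, and fatal events are also serious adverse events compared between groups. This is correct. It limits the consequence to one secondary endpoint that carries no multiplicity adjustment (SAP 6.6).

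A third reply is that no document requires the composites to be nested. That is also true, but the endpoint's name invites that reading.

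Two stronger readings are tempting. A reader might infer that every vascular death other than a stroke or MI death is censored in 9.2.6. Cases 2 and 3 above show that this is wrong. A reader might also attach a number. An assumed rate of 0.2 to 0.5% per year for case 4, applied to the 8,000 person-years in protocol 11.4.1, gives 8,000 × 0.002 = 16 to 8,000 × 0.005 = 40 deaths. The documents contain no such rate, so this range only illustrates the assumption. For scale, the planning rates over 4,000 person-years per group imply roughly 4,000 × 0.04 + 4,000 × 0.028 = 272 ischemic strokes alone.

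**Conclusion.** The concern holds in a limited form. SAP 9.2.6 and protocol 8.2 leave vascular death unnamed, and the SAP describes the category of other vascular events in two incompatible ways. A vascular death with no listed event recorded counts in 9.2.5 and is likely, though not explicitly required, to be censored in 9.2.6. The broader composite is therefore not guaranteed to contain the narrower one.

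The number of patients affected cannot be derived from the documents. The conclusion assumes only that some vascular deaths will occur without a recorded listed event and that programming follows the evaluated-event categories. It does not support a claim that such deaths are hidden from the trial: they remain in 9.2.4 and 9.2.5. The primary endpoint, the sample size and the interim rule are untouched. What could change is the result of one secondary endpoint and how it is read beside its neighbour.

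**What to change.** In protocol section 8.2 (and the protocol summary) and in SAP 2.2.2, 9.2 and 9.2.6, define the endpoint as stroke, MI, other vascular events, or vascular death. State once which causes of death are vascular, and use that classification for both 9.2.5 and 9.2.6. Align the list of other vascular events in the SAP definitions and 6.2.5 with the endpoint text: settle whether it is open or closed, where revascularization belongs, and whether the pulmonary item is embolism or thrombosis.

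No new data are needed. The cost is a minor amendment to one secondary endpoint definition. Under protocol section 18 it needs approval from the Protocol Authoring Committee, and ethics review if judged significant. It should be made before database lock, so that the handling of these deaths is not chosen with results in view.
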